**5. STUDY DESIGN**

This trial is a randomized national multicentre study comparing intensified and conventional follow-up schedule for patients after curative treatment of colorectal cancer. The inclusion is during maximal 2.5 years or until 2000 patients are included. Total expected duration 3 years. Patients may enter during their first three years after curative treatment[[1]](#footnote-2) of colorectal cancer.

The study is constructed with the stepped-wedge design. This implies a randomization at hospital level. The surgeons in a hospital control all their eligible patients according to the care as usual. At the moment determined by the randomization, all included patients will change to the intensified study follow-up protocol. As a result, the early-randomized hospitals have a large amount of patients in the study group and a small amount of patients in the control group, where in the late-randomized hospitals it is the other way around. Randomization will take place on July 1st, 2010 and randomization will be performed per two hospitals. The firstly randomized hospitals start with the intensified follow-up scheme on January 1st, 2011 and since ten hospital will participate, the last two hospitals start with the intensified follow-up scheme at January 1st, 2012.

**6. STUDY POPULATION**

## *6.1. Population (base)*

Patients with stage II, III, and IV colorectal carcinoma after curative resection (R0 resection); this includes all new patients and patients currently in follow-up, operated within three year before start study.

## *6.2. Inclusion criteria*

Patients with stage II- III –IV colorectal carcinoma after curative resection (R0 resection)

- All new patients

- Patients currently in follow-up, operated within three years before start study

- All patients need to be above 18 and capable of understanding the Dutch language

## *6.3. Exclusion criteria*

Patients with other malignancies except basocellular carcinoma of the skin

Patients not medically fit for metastasectomy

Patients with diagnosed syn- or metachronous incurable metastases at time of start study

No written informed consent

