13. REFERENCES

**1. SUMMARY**

**Title**: Computer supported CEA surveillance after curative treatment of colorectal cancer

**Aim of the study**: The aim of the current study is to develop an evidence-based guideline with standard diagnostic tools (CEA and CT scan) that results in a (cost-) effective recommendation which is applicable for all hospitals in the routine follow-up after curative treatment of colorectal cancer.

**Study design**: In the intervention group follow-up, care consists of bi-monthly CEA measurements starting three months after surgery, a yearly outpatient clinical visit and CT imaging after one and two years. Patients will be closely monitored in an outpatient setting by a frequent testing of CEA, supported by a computer-based system (CEA watch). The patients will be asked to assess their CEA value every 8 weeks. The computer-based system allows us to closely monitor the blood values and to communicate the results to the patient as soon as possible (by e-mail and/or p-mail). In case of two consecutive significant rises in CEA values, extra imaging diagnostics will be performed. In the control group the intervention is follow-up care as usual according to the Dutch national guideline. The starting point of the new regimen will be randomised among the participating clinics.

**Endpoints**: Primary outcome: increase of 15 percent of radical resected metastases in patients as expressed as the percentage of total recurrences. Secondary outcomes: overall survival time cancer specific survival time, time to recurrent disease, quality of life, and costs related to diagnostics.

**Statistics**: Increase in percentage of resected metastases from 10-25% needs 115 patients with metastases in both groups. With an expected recurrence rate of 25%, 460 patients per group are needed. After correction factor about 800 patients per group are needed.

In the economic evaluation costs of both follow-up strategies will be assessed and compared. In addition cost-utility analysis will be conducted based on Quality Adjusted Life Years (QUALY’s).

**Study duration**: The study will be conducted in three years. After a start up period of six months all eligible patients will be identified and registered. Three months later every three months a new pair of hospitals will be randomized to start the new schedule of follow-up and all registered patients will start with the intensive schedule. The last three months will be used for analysis of the data.

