
**3. OBJECTIVE**

The aim of the current study is to develop an evidence-based guideline with standard diagnostic tools (CEA and CT scan) that results in a (cost-) effective recommendation which is applicable for all hospitals in the routine follow-up after curative treatment of colorectal cancer. All patients after a curative resection of the primary tumour (including a radical resection of synchronous metastases) and fit to undergo major surgery again if needed are eligible for this study.

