## 8. METHODS

## *8.1. Study parameters/endpoints*

### *8.1.1. Main study parameter/endpoint*

Percentage of patients with curative metastasectomy of liver- and lung metastasis from colorectal carcinoma in the study period: July 2010 – October 2012.

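### Section 6.3 excludes known incurable metastases at study start but not known, still unresected, resectable metachronous ones, which probably raises the control percentage slightly.

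*Protocol*

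**What the plan says.** **Who enters.** Protocol Section 6.2 admits new patients and also "Patients currently in follow-up, operated within three years before start study". Disease status is fixed by the completed operation: "Patients with stage II- III –IV colorectal carcinoma after curative resection (R0 resection"). Section 3 makes clear that this covers stage IV patients, "including a radical resection of synchronous metastases". Neither section requires an enrolled patient to be free of recurrence at study start.

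**Who is kept out.** The only exclusion in Section 6.3 that concerns metastases is "Patients with diagnosed syn- or metachronous incurable metastases at time of start study".

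**What is counted.** Section 8.1.1 defines the main parameter as "Percentage of patients with curative metastasectomy of liver- and lung metastasis from colorectal carcinoma in the study period: July 2010 – October 2012". The Summary gives the denominator as recurrences: "radical resected metastases in patients as expressed as the percentage of total recurrences". Neither says that the metastasis must first be diagnosed after the patient is registered.

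**Which condition comes first.** Section 5 places every hospital in usual care at the outset: "The surgeons in a hospital control all their eligible patients according to the care as usual". The first pair switches on January 1st, 2011 and the last on January 1st, 2012. Section 10 compares the period before implementation with the period after it.

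**The concern.** A metastasis already known when the study opens is treated differently according to whether it can be resected. A known incurable case is removed and so never counts as a recurrence without resection. A known resectable metachronous case may stay, and once operated on it adds one to the numerator and one to the denominator. That selection can only raise the resection percentage of the condition in which it lands.

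A patient waiting for metastasectomy when the window opens in July 2010 would normally be operated on soon afterwards, while the hospital is still in its control period. The control percentage would then be raised by cases whose detection came before the comparison, and the estimated benefit of intensified follow-up would be diluted. The planned control rate is thinly supported: 10% of 115 is only 11.5 expected resections, so even a few such cases move it.

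**Working it through.** **1. The plan's own figure.** Inputs from Section 6.4: 10% versus 25% resected, 5% significance, 80% power, 115 patients with metastases per group, 25% recurrence rate, correction factor 1.71.

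- The two-sided two-proportion formula gives 113 per group with continuity correction and 100 without, so the stated 115 is reproduced to within 3% by the corrected version.
- 115 / 0.25 = 460, and 460 × 1.71 = 787, stated as about 800.

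**2. Effect of k extra cases.** Let k be the number of known, resectable, unresected metastases per 100 genuine control recurrences, of which 10 are resected under the plan. If all k are resected in the control period:

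control rate = (10 + k) / (100 + k)

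**3. A plausible range for k.** The protocol gives no prevalence. Only patients between diagnosis and operation at study start qualify. With a steady inflow,

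k ≈ 10 × (waiting time / exposure over which the 10 resections accrue)

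- Waiting time: 1 to 2 months. This is an assumption; the protocol gives no figure.
- Exposure: 12 to 36 months, also an assumption. The lower end is the average control time from July 2010 with five switch dates: (6 + 9 + 12 + 15 + 18) / 5 = 12 months. The upper end matches the three-year total duration.

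This gives k from 10 × 1/36 = 0.28 to 10 × 2/12 = 1.67. At a 25% recurrence rate that is 0.07% to 0.42% of control patients, or roughly 0.6 to 3.3 patients among 800.

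**4. Power.** With 115 per group, p₂ = 0.25 and p̄ = (p₁ + p₂)/2, ignoring clustering and continuity correction:

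power = Φ{ [p₂ − p₁ − 1.96 √(2p̄(1 − p̄)/115)] / √([p₁(1 − p₁) + p₂(1 − p₂)]/115) }

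For k = 0: (0.150 − 0.0982) / 0.0491 = 1.054, so power is 85.4%.
For k = 1.67: (0.1352 − 0.0998) / 0.0501 = 0.707, so power is 76.0%.

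| k per 100 | Control rate | Difference (points) | Power |
|---|---|---|---|
| 0 | 10.0% | 15.0 | 85% |
| 0.28 | 10.25% | 14.75 | 84% |
| 1.67 | 11.5% | 13.5 | 76% |
| 5 | 14.3% | 10.7 | 53% |
| 10 | 18.2% | 6.8 | 24% |

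**5. Check on the last two rows.** Solving the formula in step 3 for the wait, k = 5 needs 6 months (exposure 12) to 18 months (exposure 36). Against the planned 10 resections per 100 control recurrences, k = 5 means that the patients waiting on one date equal half of all planned control resections, and k = 10 means that they equal all of them. Both are unlikely.

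**The case against.** **The population is already post-R0 and in routine follow-up.** Someone diagnosed and awaiting metastasectomy is arguably in treatment: Section 7.2.1 sends patients with curable metastases on to treatment, and the one-month decision time in Section 11.2 would narrow entry further. The word incurable in 6.3 also has a sensible purpose, since a ban on any diagnosed metastasis would remove stage IV patients whose metastases were resected. This makes the gap look more like imprecise wording than intent, and it keeps the numbers small. It does not close the gap. R0 describes the operation already done (footnote 1), and Section 3 extends it only to synchronous disease. If R0 meant disease-free at entry, there would be no need in 6.3 to exclude metachronous incurable metastases.

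**Attribution to control is inferred.** This stands. The protocol does not say whether an event belongs to the period of detection or of resection, and such a rule may be in a statistical analysis plan that is not at hand. A resection delayed past a hospital's switch could count for the intervention.

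**The bias is conservative.** This also stands for cases resected in the control period: they dilute the effect and cannot create a false benefit. Dilution still costs power and distorts the cost per additional curative metastasectomy in Section 10.

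**A reader might infer that these are successes no surveillance produced.** The protocol does not support that. Control is usual care, and usual care before the study may well have found them. The defect is the selective exclusion.

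**Conclusion.** The point holds as a small, avoidable bias. Applied as written, Sections 6.2, 6.3 and 8.1.1 let known resectable metachronous metastases into the primary outcome and keep known incurable ones out. The likely direction is toward no effect.

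Under the assumed wait and exposure, the planned 15-point difference loses about 0.3 to 1.5 points, and simple unclustered power at 115 per group falls from about 85% to between 84% and 76%. This assumes that all such cases are resected in the control period; if some fall after the switch, the dilution is smaller.

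A reader might infer from larger values of k that the trial could lose most of its power. The planned 10% control rate makes those values unlikely, and the protocol gives no prevalence to support them. Nor does the point extend to synchronous metastases, which Section 3 requires to have been radically resected. The wording gap is clear; its size is not. It is worth correcting because the correction is cheap, not because the trial is threatened.

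**What to change.** - **Section 6.3:** exclude any recurrence or metastasis that is diagnosed and unresected at study start, curable or not. State that patients whose metastases were completely resected before entry remain eligible.
- **Section 8.1.1:** count only recurrences first diagnosed after registration, in both numerator and denominator.

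The second change removes these cases whichever period they would have fallen in, so it does not depend on how events are assigned to periods. Both are changes to eligibility and counting, not to patient care. The cost is one line, one clause and a few lost patients, whose metastases were found before either condition of the trial could have influenced detection. The planned 10% versus 25% and the 115 per group stay as they are.

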## *6.4. Sample size calculation*

Given current usual care with pre-operative staging with CT of the thorax and abdomen and neo-adjuvant therapies, the expected occurrence of metachronous metastases is approximately 25%. Of these, the expected percentage of resected metastases in patients is 10% in the control group and 25% in the intervention group. Given a significance level of 5% and a power of 80%, 115 patients with metastases in both groups are needed. Given an expected recurrence rate of 25%, 460 patients per group are needed.

Because in this study the moment to start the intervention instead of patients will be randomized, we calculated a correction factor C. Assuming a standard deviation in the effect of hospitals on the outcome of 0.1, C has a value of 1.71. (van Houwelingen) Therefore about 800 patients per group are needed.

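### The 80% power stated in Section 6.4 makes no visible allowance for calendar time; with time adjusted for, the planned size gives about 57–69%

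*Protocol*

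**What the plan says.** Section 6.4 of the protocol starts from the proportions: "the expected percentage of resected metastases in patients is 10% in the control group and 25% in the intervention group". It then gives the number of recurrences: "Given a significance level of 5% and a power of 80%, 115 patients with metastases in both groups are needed". These are turned into patients: "Given an expected recurrence rate of 25%, 460 patients per group are needed". The final step corrects for randomising the moment of switching instead of patients: "Assuming a standard deviation in the effect of hospitals on the outcome of 0.1, C has a value of 1.71", which leads to about 800 patients per group. The Summary repeats the chain.

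Section 5 fixes the design. Ten hospitals switch in pairs, the first on 1 January 2011 and the last on 1 January 2012. The Summary gives the step length as three months. On the hospital's date, "all included patients will change to the intensified study follow-up protocol". Recruitment has a ceiling: "The inclusion is during maximal 2.5 years or until 2000 patients are included". Section 8.1.1 counts the main outcome "in the study period: July 2010 – October 2012". Section 10 plans a comparison of care before and after the switch with a multilevel model for clustering. It mentions age, gender and tumour status as possible confounders and does not mention calendar time.

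**The concern.** Before January 2011 all hospitals are in control, and from January 2012 all are in intervention. Condition therefore tracks calendar time, and any drift in imaging, referral or surgical practice over those two years would be credited to the intervention. The staggered dates exist to separate the two, and separating them costs information. The only stated input to C is the spread between hospitals, so that cost does not appear to have been counted.

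The stated power shapes how a null result is read. If the true power for 15 points is nearer 60%, a non-significant result would be taken as stronger evidence against the schedule than it is.

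A second point bears on the same figure. The 25% recurrence rate has no horizon, yet only recurrences inside a window of about 27 months supply information. Patients enter at different times, some up to three years after surgery.

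**Working it through.** **Reproducing the plan's figures** (two-sided 5% assumed; sidedness is not stated)

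- 10% versus 25% at 80% power: 100 per group, or 113 with continuity correction. The plan has 115, which is acceptable.
- 115 / 0.25 = 460 patients per group.
- 460 × 1.71 = 787, stated as about 800. In recurrences, 115 × 1.71 = 197 per condition.
- C: within-hospital variance = (0.10 × 0.90 + 0.25 × 0.75) / 2 = 0.13875. Intraclass correlation = 0.1² / (0.1² + 0.13875) = 0.067. Recurrences per hospital per group = 115 / 10 = 11.5. Design effect = 1 + (11.5 − 1) × 0.067 = 1.71.

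The formula for C is inferred from this match. It contains no step or period term.

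**Power under the stepped-wedge model**

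The standard stepped-wedge (Hussey–Hughes) generalised-least-squares variance was used, with a random hospital effect and a fixed intervention effect. Inputs from the plan are 10 hospitals in 5 pairs, quarterly steps from January 2011 to January 2012, nine quarters from July 2010 to September 2012, hospital SD 0.1 and a difference of 0.15. The within-hospital variance is the 0.13875 above. Recurrences are assumed to be spread evenly over hospitals and quarters. Power = Φ(0.15 / SE − 1.96). The 80%-detectable difference = 2.80 × SE.

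For 1,600 distinct patients at 25% = 400 recurrences:

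| Time in the model | SE | Power | Detectable with 80% power |
|---|---|---|---|
| Nine quarterly effects | 0.0701 | 57% | 19.6 points |
| Linear trend | 0.0664 | 62% | 18.6 points |
| None | 0.0390 | 97% | 10.9 points |

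**Sensitivity**

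- Six, seven or eight periods instead of nine, 400 recurrences: 69%, 65%, 61%.
- Hospital SD from 0 to 0.15, nine periods, 400 recurrences: 67% down to 55%.
- The 2,000-patient ceiling at 25% = 500 recurrences: 66% with nine periods, and 70–77% with eight down to six.
- For 80% power: about 710 recurrences with nine quarterly effects, 632 with a linear trend, 544 in the shortest (six-period) layout.

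**Recurrence yield**

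The documents give no horizon for the 25%. Assume instead that 20%, 15% or 12.5% of 1,600 patients recur inside the window, i.e. 320, 240 or 200 recurrences. With nine quarterly effects power is 49%, 39% or 34%. By the plan's own method (C = 1.71, no time term, no continuity correction) it is 77%, 65% or 57%.

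**The case against.** The strongest reply is that the shortfall depends on a model the protocol does not state. Section 10 names clustering only, and under that model 400 recurrences give 97%, well above 80%. A separate analysis plan could also add a time term. The first part is correct as arithmetic, so it would be wrong to say without condition that 80% is not delivered. But the 97% belongs to an estimate that cannot tell the intervention from calendar time, and a time term added elsewhere would leave the power figure in Section 6.4 uncorrected.

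The formula behind C is also an inference. That stands. The power calculations above do not use C, however, so the conclusion does not depend on how it was derived.

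Three stronger readings are tempting, and the documents do not support them.

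- *The 25% is counted twice because patients appear in both groups.* If the two 800s are 1,600 distinct patients and 25% recur in the window, there are 400 recurrences, about 200 per condition, against the 197 needed. Nor is everyone's follow-up split: patients enrolled after their hospital switches contribute to intervention only. The point that remains is that the protocol does not say the 800s are distinct. If the same 800 were meant, 200 recurrences would be expected, about 100 per condition, and power would be 57% by the plan's own method.
- *1,600 contradicts 2,000.* Section 5 gives a recruitment ceiling and Section 6.4 a requirement. A ceiling above the requirement is headroom.
- *C should be larger because it was evaluated before inflation.* That formula ignores the comparison within hospitals. Clustering without time effects leaves ample power here.

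A low yield is possible but not shown. Section 2.1 quotes 30–50% metachronous metastases, so the yield could be higher. Even so, reaching 80% with nine quarterly effects would need 710 / 1,600 = 44% to recur inside the window (544 / 1,600 = 34% in the shortest layout).

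**Conclusion.** The power statement is wrong as written. The chain of figures is arithmetically sound, but 80% fits neither available model. At 400 recurrences the trial has about 97% nominal power for a time-confounded estimate, or about 57–69% once calendar time is adjusted for, depending on the time model. At the 2,000-patient ceiling the adjusted figure is about 66–77%. No time-adjusted layout tried reached 80% at either size. With nine quarterly effects and 400 recurrences the detectable difference is about 20 points. If only 12.5–20% of 1,600 patients recur in the window, adjusted power with nine quarterly effects is about 34–49%; that range is an assumption.

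The results rest on a two-sided 5% test, a normal approximation, evenly spread recurrences, a hospital SD of 0.1 unless varied, and 1,600 or 2,000 distinct patients. Having only ten clusters would lower power somewhat further.

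**What to change.** - Section 10: include calendar time in the primary multilevel model and state its form.
- Section 6.4 and the Summary: state the number of recurrences expected between July 2010 and October 2012, with the horizon of the 25%.
- Same places: give power and detectable difference from the time-adjusted stepped-wedge model for 10 hospitals in 5 steps (about 57–69% for 15 points at 400 recurrences; about 20 points detectable with nine quarterly effects), with the range over the recurrence yield.
- Say whether 800 per group means distinct patients.

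This is a rewrite of one paragraph, its summary and one sentence of the analysis section. It asks for no extra patients. The cost is a less favourable stated power, and a wider interval than a model without time would give.

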**7. TREATMENT PERIODS**

*7.1. Control period*:

Outpatient clinic at 3 months after end of treatment (surgery or adjuvant chemotherapy)

Assessment for fitness to undergo metastasectomy[[2]](#footnote-3)

Care as usual according to the Dutch guidelines ([www.oncoline.nl](http://www.oncoline.nl/)) and local amendment. The actual care as usual given may differ per hospital. Herefore, the standard care as usual per hospital will be described.

Filling out the questionnaire “SF-12 “ after 12 months

*7.2. Intervention period*:

Outpatient clinic at 3 months after end of treatment (surgery or adjuvant chemotherapy)

Assessment for fitness to undergo metastasectomy2

During year 1

CEA measurement every 8 weeksatlocal laboratory, report results by letter. The possibilities for blood sampling at a local laboratory are now examinated per hospital. The measurement will take place at the hospital itself, samples will be mailed to the laboratory.

If no special events occur, no additional out patient clinic visits

At year 1 helical CT-abdomen[[3]](#footnote-4) and colonoscopy[[4]](#footnote-5)

Filling out the questionnaire “SF-12 “ after 12 months

Filling out the questionnaire of intensified follow-up at 1 year

One year after surgery outpatient clinic visit

- Results from evaluation (CT) and evaluation long term surgical results

- Update assessment for fitness metastasectomy

During year 2

CEA measurement every 8 weeks atlocal laboratory, report results by letter

If no special events occur, no additional out patient clinic visits

At year 2 helical CT thorax/abdomen4

Two years after surgery outpatient clinic visit

Results from evaluation (CT) and evaluation long term surgical results

Update assessment for fitness metastasectomy

During year 3

CEA measurement every 12 weeks atlocal laboratory, report results by letter

If no special events occur, no additional out patient clinic visits

At year 3 helical CT thorax/abdomen

Three years after surgery outpatient clinic visit

Results from evaluation (CT) and evaluation long term surgical results

Update assessment for fitness metastasectomy

All patients will be informed about the laboratory results by letter or email. In case of positive results patients will be invited to undergo a CT scan followed by an outpatient clinic visit. All patients will have access to the surgeon’s outpatient clinic in case of questions or clinical complaints.

*7.2.1.Procedure when CEA crosses the threshold value (see flowchart, addendum 2)*

Increase > 20% in 8 weeks > repetition of CEA measurement in 4 weeks, also measuring CRP level.

Increase in second measurement after 4 weeks > 10%, with a lower static threshold value of 2.5 ng/ml > outpatient clinic visit; if explanation of rise is clear from clinical reasons (ie., active infection): treat infection and re-assess CEA value after 4 weeks. If increase:

-> Evaluation by helical CT Thorax/abdomen within two weeks:

-> Outpatient clinic within 7 days after CT scan

At this visit an assessment is made evaluating

- The presence of resectable metastasis in liver or lung

- Physical signs suggesting other localizations of recurrent disease

- Fitness of the patient to undergo treatment of metastasis

When curable metastases are found and the patient can undergo metastasectomy

-> Treatment at own or referral centre according to the current standard

When irresectable metastases are found or the patient is unfit to undergo metastasectomy

-> Referral to medical oncology for palliative chemotherapy according to the current standard;

-> Referral to radiotherapy when palliative radiation is clinically considered

When no liver and lung metastases are found on CT scan

-> CEA measurement as before

-> Next step dependent on outcome, to discuss in interdisciplinary platform

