## *Study procedures*

## Vena puncture bi-monthly: measurement serum CEA and serum ‘in storage’

## Vena punctures are carried out at local laboratories.

## CT scan abdomen/thorax

## At year 1 (abdomen) and 2 (thorax/abdomen)

## If CEA rises as outlined in the flowchart, a CT scan thorax/abdomen will be performed because of the suspicion for local recurrence or metastatic disease. If this scan is made coincidently at or around year 1, 2 or 3, the standard scan will be cancelled.

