2. Only when the patient is fit enough for metastasectomy, follow-up is started. This is assessed at the first outpatient visit and if necessary delayed at the surgeon’s judgment. [↑](#footnote-ref-3)
3. When a patient underwent a CT thorax/abdomen due to a rise in CEA during follow-up, the study CT at year 1 and 2 will not be made. [↑](#footnote-ref-4)
4. When a full colonoscopy has been performed pre-operatively, the colonoscopy at year 1 is not indicated. [↑](#footnote-ref-5)

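### Two intervention schedules compete for year 3, and Section 7.2 states none for patients already past month 36 when their hospital switches

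*Protocol*

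**What the plan says.** Section 7.2 is the only year-by-year intervention schedule. It sets CEA every 8 weeks in years 1 and 2. For year 3 it sets "CEA measurement every 12 weeks atlocal laboratory, report results by letter" and "At year 3 helical CT thorax/abdomen". It places its visits one, two and three years after surgery and stops there.

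The summary (Section 1) describes the intervention as bi-monthly CEA with "a yearly outpatient clinical visit and CT imaging after one and two years". It adds: "The patients will be asked to assess their CEA value every 8 weeks". It makes no exception for year 3.

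The study procedures in Section 8 give "Vena puncture bi-monthly: measurement serum CEA and serum" storage, again without a year-3 exception, and list the scheduled CTs as "At year 1 (abdomen) and 2 (thorax/abdomen"). The same text then says of a scan made because CEA rose: "If this scan is made coincidently at or around year 1, 2 or 3, the standard scan will be cancelled". Footnote 3 to Section 7.2 has the matching rule without year 3: "the study CT at year 1 and 2 will not be made".

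Sections 6.1 and 6.2 admit patients operated up to three years before study start. Section 5 moves every included patient of a hospital to the new schedule at that hospital's switch, between January 2011 and January 2012. Section 2.3 reports the Dutch guideline as CEA every 3 to 6 months for three years and six-monthly in years 4 and 5.

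**The concern.** The trial compares two follow-up schedules, so the intervention schedule is the treatment. For year 3, a hospital cannot tell from the protocol whether to test every 8 or every 12 weeks, or whether to make a third CT. After month 36, Section 7.2 gives no schedule at all, while nothing in Section 5 or 6 stops those patients from switching and being counted. The tests delivered, and with them the contrast and the costs generated, could then differ between hospitals because of the wording alone.

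There is also a structural effect. A stepped-wedge trial that carries a fixed set of patients forward places its intervention time later after surgery than its control time, if patients stay in. Adjusting for hospital clustering does not remove that difference.

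**Working it through.** The protocol gives no figure of its own on this point, and the sample size is not affected.

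**1. Year 3, side by side**

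| Source | CEA in year 3 | CT at year 3 |
|---|---|---|
| Section 7.2 | every 12 weeks | yes |
| Summary | every 8 weeks / bi-monthly | no (years 1 and 2) |
| Study procedures, list | bi-monthly | no (years 1 and 2) |
| Study procedures, cancellation rule | not addressed | presupposed |
| Footnote 3 to Section 7.2 | not addressed | not named |

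The summary and the list in the study procedures agree with each other. There are thus two schedules, plus one internal conflict about the scan.

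**2. Tests per year.** 52/12 = 4.3 or 52/8 = 6.5. The guideline gives 2 to 4 in year 3. The ratio to control is 4.33/4 = 1.1 to 4.33/2 = 2.2 under Section 7.2, or 6.5/4 = 1.6 to 6.5/2 = 3.3 under the other text. Scheduled CTs over three years: three or two.

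**3. Oldest patient at the switch.** Ten hospitals in pairs, with first and last switch in January 2011 and January 2012, give quarterly steps s = 6, 9, 12, 15 and 18 months after July 2010. The oldest eligible patient is at 36 + s = 42, 45, 48, 51 and 54 months. If study start means January 2011, the figures are 36, 39, 42, 45 and 48. This step needs no assumption about surgery dates.

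**4. Illustration of scale.** Assumptions: one surgery per month per hospital pair, before and after study start; entry 3 months after surgery; no attrition; study start July 2010; end October 2012 (month 27). At month t a pair then has 33 + t patients in follow-up, of whom t are past month 36 and, from the first switch on, 12 are in year 3.

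- Intervention person-months: Σ[33(27 − s) + (27² − s²)/2] = 1039.5 + 918 + 787.5 + 648 + 499.5 = 3892.5.
- Of these, past month 36: Σ(27² − s²)/2 = 1417.5, or 36%.
- Of these, in year 3: 12 × Σ(27 − s) = 12 × 75 = 900, or 23%.
- Control person-months: Σ(33s + s²/2) = 2385; past month 36: Σs²/2 = 405, or 17%.
- Mean time since surgery: 29.2 months in intervention, 23.1 in control.

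With a January 2011 start, intervention time is 27 × 75 + 1417.5 = 3442.5, of which 900 (26%) is in year 3 and 1417.5 − 6 × 75 = 967.5 (28%) is past month 36. Control then has 7% to 12% past month 36, depending on whether control time is counted from July 2010 or January 2011. Adding exits at 25% per 36 months to the January start gives 50% of intervention time in year 3 or later. Cutting new accrual to 30% under the July start gives 75%.

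**5. If follow-up stops at month 36.** Everyone then lies between months 3 and 36. With equal accrual the mean is (3 + 36)/2 = 19.5 months in both periods, and 12/33 = 36% of intervention time is still in year 3. With new accrual at 50% or 30% of the earlier rate, the means are 21.9 v 20.3 and 23.4 v 20.7 months.

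**The case against.** The best reply is that Section 7.2 governs, because it alone is laid out by year and the cancellation rule in the study procedures supports its year-3 CT. That makes Section 7.2 the natural default. It does not remove the conflict: the summary may pass as shorthand, but the study procedures are operative text.

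A second reply is that protocol follow-up simply ends at the three-year visit, since Section 5 limits entry to the first three years. This is a fair reading, and with equal accrual it removes the imbalance in time since surgery. But no sentence says it, and Section 5 switches all included patients without a cap. Year 3 would still be unsettled.

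A reader might infer several stronger points that the documents do not support:

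- **That the CEA trigger cannot operate in year 3.** Section 7.2.1 words it as a 20% rise over 8 weeks; over 12 weeks the same growth rate is 1.2^(12/8) = 1.31, a 31% rise. But that section refers to a flowchart in addendum 2, which is not in the text at hand, and the summary words the rule without an interval. Only a check is warranted.
- **That the costing is invalid.** Section 10 registers volumes per patient (travel excepted), so delivered tests are counted whatever the schedule says. The wording affects what is delivered.
- **That the model excludes time since surgery.** Section 10 gives age, gender and tumour status as examples only.
- **That the contrast vanishes.** The ratio of 1.1 needs controls at the guideline maximum. The survey in Section 2.6 reports six-monthly CEA after year 1, at which year 3 is 2.2 or 3.3 times control.
- **That intensified patients would be tested less than controls after month 36.** Section 7.2 is silent there, which is not an instruction to stop, and the 8-weekly wording elsewhere has no end date.

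**Conclusion.** The point holds as two competing year-3 schedules and an unstated schedule after month 36. The contradictions and the 42 to 54 months (36 to 48 with a January 2011 start) follow from the text and its dates, with quarterly steps. So do 4.3 or 6.5 CEA tests per year against 2 to 4, and three or two CTs.

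The person-time shares of 23% in year 3 and 36% v 17% past month 36 are illustrative. They rest on even surgery dates, equal accrual, no attrition and a July 2010 start, and the protocol gives no distribution of surgery dates. Person-time is also not the denominator of the resection percentage, which the summary and sample size section take among patients with recurrence. It would therefore be wrong to read these shares as a bias: neither its direction nor its size can be derived. The correction should be made because it is cheap and settles what the trial tests.

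**What to change.** 1. Make the summary, the study procedures and footnote 3 match one year-3 schedule, with Section 7.2 as the natural default. Check that the Section 7.2.1 trigger and the addendum 2 flowchart fit the CEA interval used in year 3. This is wording only.
2. Either end each patient's contribution at month 36 in both periods, or state the intervention schedule after month 36. The clinical investigators should choose. Under the assumptions above, ending at month 36 gives up about 36% of intervention and 17% of control person-time. Stating a later schedule adds tests for those patients.
3. Add time since surgery to the confounders named for the Section 10 multilevel model. Measure it at the patient's entry into each period and not at recurrence, whose timing the intervention can change. It uses the surgery date already needed for eligibility and costs a few degrees of freedom with ten hospitals. It keeps its use if follow-up stops at month 36 and accrual is not steady.
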